### Analysis

#### Analysis plan and sample size for objective 1

##### Independent variables for objective 1

For the variables in objective 1, it is important to understand that the intervention is applied to the healthcare providers, but the unit of analysis for the outcomes is episodes of bacteriuria occurring in catheterized inpatients (Table 3). We will account for the correlation that may exist among patients treated by the same healthcare provider in our regression models. The independent variables include age and gender of the patient, duration of catheter use, catheter type, hospital ward and service, types and quantities of organisms found in the urine, number of white blood cells (WBCs) in urine, number of WBCs in the serum, and highest temperature in 24 hours around the time of urine specimen collection.

##### Dependent variables for objective 1a--inappropriate treatment

The main outcome of interest for this objective is the number of cases of ABU that are managed inappropriately out of all episodes of bacteriuria. This determination will be made by applying the diagnostic algorithm. The dependent variable to be used in the analytic models will be whether or not each episode of bacteriuria is managed inappropriately. The unit for analysis will be episodes of bacteriuria.

A secondary outcome will be the number of days that antibiotics are given to treat ABU. We will determine the reason for treatment of bacteriuria (if stated in the medical record), antibiotics given, and duration of treatment. As a safety issue, we will monitor outcomes of bacteriuria at both sites for 30 days following the episode. These outcomes will include any side effects of the antibiotics given, isolation of an organism resistant to the antibiotics given, or *Clostridium difficile *colitis. We will also monitor for any complications that may develop from bacteriuria, such as symptomatic UTI, pyelonephritis, and urosepsis.

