Distributing this guidelines-based algorithm will address both awareness and familiarity, but guideline dissemination alone is not an effective method to achieve guideline implementation [18,19,24-26]. The audit and feedback intervention will tackle two points in the chain of events that leads from a patient at risk to a patient who receives unnecessary antibiotics for ABU: the decision to order a urine culture (inappropriate screening) and the decision to treat a positive urine culture (inappropriate prescribing). We can measure the clinical outcomes after each of these points (objective 1); at the same time, we can measure changes in providers' knowledge (awareness and familiarity) and attitudes (social norms, acceptance, risk perceptions, self-efficacy, and outcome expectancy of ABU guidelines) (objective 2). The algorithm itself and the instructions on how to use it (via audit and feedback) will address self-efficacy concerning the guidelines. Lack of outcome efficacy will also be addressed through the audit and feedback sessions, as clinicians will be reassured when they see that withholding inappropriate antibiotics does not lead to harm and may even benefit their patients. We expect agreement with and acceptance of guidelines to likewise increase. We will also identify external barriers to guideline compliance by performing exit interviews with clinicians who have participated in the study. The conceptual model depicted in Figure 1 will enable us to determine which aspects of our implementation protocol are responsible for the observed changes in clinical outcomes.

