#### Patients participating in the study

All patients in the targeted study wards at the two sites are indirectly participating in the study through our surveillance for relevant clinical outcomes. Year 1 of the study began in July 2010, so we are currently in the baseline surveillance phase. Reviews of the medical records are performed for all patients in the study wards at both sites five days per week; weekend surveillance results are captured backwards from Monday's findings. This review is performed using the VA electronic medical record, the Clinical Patient Record System (CPRS). Information collected includes bed-occupancy days, presence of any type of urinary catheter (indwelling or Foley, external or condom, intermittent, and suprapubic), whether a urine culture was sent, and the results of any urine cultures sent. Bedside visits are made in one ward per month to verify the catheter presence and type reported in the electronic medical record. Additional information is collected for each episode of bacteriuria (≥10^3 ^organisms/mL of urine). For each episode of bacteriuria, we collect information about patient demographics, the presence/absence of relevant symptoms and comorbidities, and type/duration of antibiotics given. We use this information to classify episodes of bacteriuria as ABU or CAUTI and to determine whether the provider's response to the urine culture results was appropriate or inappropriate. Surveillance data are stored in Excel (Microsoft Corporation, Seattle, WA, USA), while the individual episodes of bacteriuria are detailed in an Access database (Microsoft Corporation, Seattle, WA, USA), which also uses a computer query to verify our case classification. We use Theradoc^® ^(Hospira, Inc., Salt Lake City, UT, USA), a proprietary infection-control software package used in several VA hospitals, to extract the information about antibiotic usage from CPRS.

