#### Outcomes

Objective 1 focuses on the clinical outcomes of inappropriate screening for and treatment of catheter-associated ABU, as well as on complications of inappropriately prescribed antibiotics (Table 3). Objective 2 focuses on measuring changes in knowledge and attitudes concerning the ABU and CAUTI guidelines (see Table 2).

**Table 3 T3:** clinical outcomes for objective 1 in order of importance

Outcomes	**Measurement of change**^**a**^
Inappropriate treatment of CAABU	Fewer episodes of CAABU treated inappropriately

Inappropriate collection of urine cultures from patients with CAABU	Decreased number of urine cultures/1,000 catheter-days

Number of days antibiotics given for CAABU	Fewer days of antibiotic use for CAABU

Use of urinary catheters	Decreased urinary catheter-days/patient bed-days

Complications of inappropriate antibiotics	*Clostridium difficile *colitis, emergence of resistant organisms^b^

Complications of bacteriuria	No increase in pyelonephritis or urosepsis

^a^Comparisons are for the specific wards on the intervention facility and the corresponding wards on the control facility. ^b^In 30 days following inappropriate antibiotic use in a given patient.

CAABU = catheter-associated asymptomatic bacteriuria.

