##### Dependent variables for objective 1b--inappropriate screening

For this objective, we are interested in whether the intervention results in decreased screening for ABU in catheterized patients. Screening for catheter-associated ABU will be measured by the number of urine cultures collected per days of catheter use. We predict that as healthcare providers become more comfortable with leaving catheter-associated bacteriuria untreated, they will recognize that urine cultures are frequently unnecessary in catheterized patients and thus, order fewer urine cultures. All urine cultures sent to the microbiology laboratory from the study units will be documented, whether positive or negative. We will calculate the number of urine cultures collected per 100 catheter device-days for each unit.

A secondary outcome for objective 1b will be the frequency of use of urinary catheters in hospitalized patients. We will need to track this information, as our intervention may have the unintentional but beneficial effect of causing providers to remove unnecessary urinary catheters. Therefore, we will also calculate the number of catheter device-days per 100 patient bed-days on each unit.

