##### Estimated sample size for objective 1b--inappropriate screening

We do not have estimates of the percentage of catheterized patients who are screened for ABU. We have based our estimates of the sample size on detecting a reduction in the intervention group of 25% in the percentage of catheterized patients who are screened for ABU. Based on estimates of the number of catheterized patients at Houston and San Antonio in a one-year time period (1,867 and 1,512, respectively), we will have 80% power to detect a 25% reduction in percentage of patients screened, even if the percentage of screened patients is as low as 10%.

#### Analyses for objective 1

For the analysis of inappropriate treatment, we will test for differences in the proportion of inappropriately treated episodes of bacteriuria between intervention and control sites using a hierarchical regression approach. Episodes will be nested within patients and patients nested within provider. Independent variables will be those described above. A significant value for the parameter estimate for the intervention will indicate that the audit feedback group differed from the control group.

For the analysis of inappropriate screening, we will conduct a logistical regression analysis in which the dependent variable will be whether or not the catheterized patient received screening for ABU. Hierarchical models will allow nesting of patients within provider. An indicator variable for the intervention effect will be used to determine differences between the audit feedback and control groups. Independent variables will include variables to indicate the unit in which the patient was hospitalized in addition to patient-related characteristics. A similar logistical analysis will be run for the secondary outcome of whether or not the hospitalized patient had a urinary catheter. For both the primary and secondary outcomes, the number of cultures per 100 device-days and the number of device-days per 100 bed-days will be compared among the units using analysis of covariance.

For the secondary outcome of days of inappropriate antibiotic use, we will first examine the distribution of the number of days that antibiotics were given. If the distribution is not normally distributed, we will consider appropriate transformations. In addition, we may consider use of hierarchical Poisson regression models.

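### The objective 1a proportion is taken over culture-detected bacteriuria, which the intervention is meant to reduce, so it neither isolates the treatment decision nor tracks total inappropriate antibiotic use

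*Protocol article*

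**What the plan says.** In the protocol article, the section on dependent variables for objective 1a sets the main outcome as "the number of cases of ABU that are managed inappropriately out of all episodes of bacteriuria" and adds: "The unit for analysis will be episodes of bacteriuria". In the section on analyses for objective 1, a hierarchical regression will "test for differences in the proportion of inappropriately treated episodes of bacteriuria between intervention and control sites".

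Episodes come from chart surveillance. The section on patients participating in the study lists among the data collected "whether a urine culture was sent, and the results of any urine cultures sent", and describes no cultures taken for the study itself.

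The conceptual framework names two targets of audit and feedback: ordering a culture and treating a positive one. The section on dependent variables for objective 1b predicts that as providers become comfortable leaving bacteriuria untreated, "they will recognize that urine cultures are frequently unnecessary in catheterized patients and thus, order fewer urine cultures". The sample size for objective 1b is based on a 25% reduction in the percentage of catheterized patients screened.

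Objective 1a itself is a hypothesis about less inappropriate antibiotic use for catheter-associated ABU (CAABU). Table 3 words the outcome as "Fewer episodes of CAABU treated inappropriately", with no denominator.

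**The concern.** If objective 1b succeeds, fewer bacteriuria episodes are detected at the intervention site, and those that remain are a different mix. The 1a analysis then compares sites on a set of episodes that the intervention has helped to select. Neither the control site nor the baseline year removes this, because the selection arises at the intervention site during the intervention.

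A proportion on this denominator answers neither of two separate questions. One is whether providers treat a detected ABU less often. The other is whether patients receive fewer inappropriate courses. The second is what the objective 1a hypothesis is about, and the proportion can move differently from it.

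**Working it through.** **The plan's own figure.** The sample-size section gives 36% against 25%, two-sided α = 0.05, 80% power and 300 episodes per site. The arcsine values reproduce: φ₁ = 1.287, φ₂ = 1.047, h = 0.2398. The stated formula, n = 2((1.960 + 0.842)/h)², gives 273. A comparison of two proportions gives 274, or 292 with continuity correction. Power at 300 per site is about 83.5%. The sample size is not in dispute.

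**Inputs for the denominator check.**
- Baseline proportion 36% (sample size for 1a), that is, 360 inappropriately treated per 1,000 episodes.
- A 25% cut (sample size for 1b). The protocol states it for the percentage of patients screened; applying it to detected episodes is my assumption.
- ABU share of episodes, a: not given, assumed 0.5 to 0.8. The share of ABU treated is then 0.36/a, that is, 0.72 to 0.45.
- Catheter-days and bed-days held fixed. Every episode still cultured is treated as it would have been before.

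**Results per 1,000 baseline episodes.**

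| What is no longer cultured | 1a proportion, a = 0.5 | 1a proportion, a = 0.8 | Inappropriate courses |
|---|---|---|---|
| A. 25% of ABU, regardless of treatment | 270/875 = 30.9% | 270/800 = 33.8% | 270 (-25%) |
| B. 25% of all episodes | 270/750 = 36.0% | 270/750 = 36.0% | 270 (-25%) |
| C. The same number of ABU, all of which would have gone untreated | 360/875 = 41.1% | 360/800 = 45.0% | 360 (no change) |
| D. The same number of ABU, all of which would have been treated | 235/875 = 26.9% | 160/800 = 20.0% | 235 or 160 (-35% or -56%) |

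A and B have the same fall in courses but different proportions. In C the proportion worsens while courses do not change.

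**Could culturing alone produce the planned effect?** In case A, let x be the ABU still detected, as a share of baseline episodes. Solve x(0.36/a)/(x + 1 - a) = 0.25, which gives x = 0.25(1 - a)/(0.36/a - 0.25).
- a = 0.5: x = 0.125/0.47 = 0.266, a fall in ABU detections of 1 - 0.266/0.5 = 47%.
- a = 0.8: x = 0.05/0.20 = 0.25, a fall of 1 - 0.25/0.8 = 69%.

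**Could a real reduction be hidden?** A fall from 360 to 250 courses would show as a flat 36% if episodes fell from 1,000 to 250/0.36 = 694.

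**CAABU episodes as denominator.** The proportion of detected ABU treated stays at 72% (a = 0.5) or 45% (a = 0.8) in A and B. In C it rises to 360/375 = 96% or 360/600 = 60%, although no provider treats any episode differently. This denominator is closer to the prescribing decision, but it too has to be read beside the detection rate.

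**The case against.** The strongest reply is that a fall in the proportion through less culturing is no false benefit. In case A, inappropriate courses really do fall by 25%, and the intervention is meant to work through culture ordering as well as treatment. This stands. A reader might infer that the trial could report a benefit with nothing gained for patients, or that the 1a result would be meaningless. The documents do not support either. What the proportion cannot do is say which decision changed, or by how much total misuse fell.

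A reader might also infer that less culturing could by itself deliver the planned 36%-to-25% effect. At the protocol's own 25%, case A moves the proportion by about 2 to 5 of the 11 points. With 300 episodes per site, such a shift alone would reach significance only about 8% to 27% of the time. Only an avoidance concentrated on ABU that would have been treated (case D) comes near the target, and there courses fall sharply too.

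Case B needs symptomatic and asymptomatic detections to fall alike, which is less plausible than a selective fall. It marks one end of the range and is not a forecast.

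Objective 1b measures culturing separately, so a shift would be visible. The planned covariates (temperature, white cell counts, organisms) adjust partly for case mix. Both points are fair, but neither repairs 1a: 1b does not change its denominator, and covariates measured around a culture cannot restore episodes never cultured.

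Finally, one might read Table 3, the 1a definition and the sample-size text (which speaks of a percentage of patients) as three rival outcomes. That goes too far. The analysis sections consistently use the episode; the rest is loose wording to be aligned.

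**Conclusion.** The concern holds as a structural point. By the protocol's own prediction, the denominator of the main outcome is affected by the intervention at one site. With an assumed ABU share of 0.5 to 0.8, a 25% cut in detections and unchanged treatment of what is still cultured, the proportion can be about 31%-34%, 36% or 41%-45%, depending on which cultures are avoided. Inappropriate courses fall by 25% in the first two cases and not at all in the third. If avoidance is unrelated to whether the ABU would have been treated, reaching 25% through culturing alone would take a fall in ABU detections of about 47%-69%.

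The existence of the problem does not depend on the assumed share; its size does. The direction cannot be known in advance.

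**What to change.** The article places the study in its baseline year, so this can be settled before the intervention starts.

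- Specify inappropriately treated CAABU episodes per 1,000 patient bed-days, compared by site and period, as the measure of total inappropriate treatment. Make it primary, or report it together with the primary. Bed-days are preferable to catheter-days because the protocol notes that "our intervention may have the unintentional but beneficial effect of causing providers to remove unnecessary urinary catheters".
- Keep the episode-level hierarchical model for the prescribing decision, with CAABU episodes as denominator. Report it beside CAABU episodes detected per 1,000 bed-days.
- Use the same definitions in Table 3, the 1a outcome section and the 1a sample-size section.

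The data cost is small: bed-occupancy days, cultures and treated episodes are already collected. There are two drawbacks. The bed-day rate combines catheter use, culturing and prescribing, so it must be read with the proportion. The protocol also gives no event rate, so the planning value has to come from year-1 surveillance and the 36%-to-25% basis has to be restated if the rate becomes primary. Replacing the hierarchical model altogether with ward-level counts is not needed and would lose the episode-level covariates.

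### Follow-up for urinary complications starts at a positive culture, which the intervention is meant to make rarer, so a per-episode safety comparison could mislead in either direction

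*Protocol article*

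**What the plan says.** The safety follow-up is described under the dependent variables for objective 1a: "we will monitor outcomes of bacteriuria at both sites for 30 days following the episode". The harms of leaving bacteriuria untreated are listed there too: "We will also monitor for any complications that may develop from bacteriuria, such as symptomatic UTI, pyelonephritis, and urosepsis". Table 3 in the Outcomes section states the criterion as "No increase in pyelonephritis or urosepsis", with no denominator, rate or margin.

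The section on participating patients defines an episode by an organism count in urine, so it needs a culture. Clinical detail follows from that: "Additional information is collected for each episode of bacteriuria", and symptoms are among the items abstracted for those episodes. For other ward patients the same section lists bed-days, catheter presence and type, whether a culture was sent, and its result. The section on independent variables for objective 1 states that "the unit of analysis for the outcomes is episodes of bacteriuria occurring in catheterized inpatients", with a reference to Table 3.

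Objective 1b predicts that as providers become comfortable with leaving bacteriuria untreated, "they will recognize that urine cultures are frequently unnecessary in catheterized patients and thus, order fewer urine cultures". Its sample-size paragraph plans for a 25% reduction in the percentage screened in the intervention group.

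**The concern.** If safety follow-up opens only with a positive culture, and the intervention lowers the number of cultures, then the set of patients followed for harm is formed after the intervention starts and is partly produced by it. The two sites, and the years before and after, would then be compared on differently selected patients.

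This bears on the harm that a study of less culturing and less treatment most needs to rule out: an infection recognised late in a patient who was not cultured. The conceptual framework expects clinicians to be reassured that withholding unneeded antibiotics does no harm, and the Discussion looks ahead to dissemination. Both lean on this outcome. A per-episode rate could look flat while harm per catheterised patient rises, or could rise with no real harm because the episodes left are the more symptomatic ones.

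**Working it through.** The article gives no complication rate, margin or sample size for this outcome, so there is no stated figure to reproduce. The check is of the logic, followed by an illustration.

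**Routes into the safety count for a patient who is not screened**

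- *Falls ill, then has a positive culture on a study ward.* The culture is recorded, symptoms are abstracted and the episode is classified as CAUTI. The event is in the database. Whether it counts towards the Table 3 criterion, being itself the index episode and not something that followed one, is not stated.
- *Falls ill and is never cultured, or is culture-negative after antibiotics.* No route is described.
- *Falls ill after transfer or discharge with no earlier episode.* No 30-day window was opened, and no route is described.

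**Illustration**

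From the article (sample size for objective 1b): 1,867 catheterised patients a year at the Houston site, and a planned reduction c = 25%.

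Assumed: 20% have a positive culture at baseline; 3% of those have an event; the cut in screening carries over in proportion to positive cultures; patients no longer cultured have k times the baseline risk. Ranges shown: c from 10% to 40%, k from 1 to 2.

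Baseline: 1,867 × 0.20 = 373 followed; 373.4 × 0.03 = 11.2 events; 11.2 / 1.867 = 6.0 per 1,000 catheterised patients.

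After a 25% cut: 93 patients leave follow-up and 280 remain.

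*Direction 1, harm missed.* Events per 1,000 among the patients who would have been followed at baseline = 6.0 × (1 − c + c × k):

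| Cut in culturing | k = 1 (3%) | k = 1.5 (4.5%) | k = 2 (6%) |
|---|---|---|---|
| 10% | 6.0 | 6.3 | 6.6 |
| 25% | 6.0 | 6.75 | 7.5 |
| 40% | 6.0 | 7.2 | 8.4 |

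If none of the events in the patients no longer cultured is counted, the per-episode rate is 3% in every cell, and the event count falls from 11.2 to 10.1, 8.4 or 6.7 for the three cuts.

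That is the extreme case. For c = 25% and k = 2, the uncultured patients have 93.35 × 0.06 = 5.6 events. If a fraction f of these is later cultured and counted, the total counted is 8.4 + 5.6 × f, from 8.4 (f = 0) to the full 14.0 (f = 1). The text does not settle f.

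*Direction 2, false alarm.* Suppose the patients no longer cultured would have had no events, and still have none. Events stay at 11.2, but the per-episode rate becomes 3% / (1 − c): 3.3%, 4.0% and 5.0% for cuts of 10%, 25% and 40%. For the 25% cut, 11.2 / 280 = 4.0%.

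**The case against.** Several points on the other side have force.

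1. *The per-episode rate is an inference.* Table 3 gives no denominator, its footnote compares wards with corresponding wards, and its 30-day footnote is attached only to the row on complications of antibiotics. Table 3 also lists cultures per catheter-days and catheter-days per bed-days, so the statement that the unit of analysis is the episode cannot be literal for every row. This stands as a caution. Even so, the 30-day window is tied to the episode in the text itself, and the article extends the hierarchical regressions to the remaining Table 3 outcomes where possible.

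2. *Sick patients get cultured.* A reader might infer that an unscreened patient who becomes septic and is then cultured still does not count. No passage says so. Charts are reviewed on a regular cycle ("Reviews of the medical records are performed for all patients in the study wards at both sites five days per week"), and such a patient enters as CAUTI. What remains is that the text does not say these episodes count, and that events without a positive culture on a study ward have no described route.

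3. *The numbers are assumed.* They are. The Background also says that treating catheter-associated ABU improves neither morbidity nor mortality and does not reduce symptomatic CAUTI, which argues against a doubled risk. At a 25% cut the illustration amounts to 14.0 events against 11.2, fewer than three extra, which would be hard to detect on any denominator.

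4. *Catheter-days would not cure the problem.* Objective 1b allows that the intervention may lead to catheters being removed, and Table 3 lists fewer catheter-days as a wanted change. This stands, and is why bed-days are preferred below.

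5. *A condensed article may leave counting rules to the full protocol.* That would excuse silence on detail. The start of follow-up and the trigger for data collection are stated here, and they are what creates the problem.

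**Conclusion.** Entry to safety follow-up, as described, depends on a positive culture, and the intervention is intended to change how often cultures are taken. A comparison per episode could therefore mislead in either direction and would not be a sound basis for concluding that complications did not increase.

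Two stronger readings are not supported. Harm in patients no longer cultured is not wholly invisible, because those later cultured positive on a study ward are recorded. Nor is the shift confined to one site: the algorithm is distributed at both, so the change is expected mainly, not only, at the intervention site.

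The size is hypothetical. With the assumed 20% and 3%, a 25% cut in culturing is compatible with a flat 3% per-episode rate while events go from 6.0 to 7.5 per 1,000 catheterised patients (k = 2, none of the missed events counted), and equally with a rise to 4.0% per episode and no change in events. This is a weakness in a secondary safety measure. It does not touch the primary comparison of inappropriate treatment.

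**What to change.** Define the Table 3 outcome as all pyelonephritis and urosepsis, and symptomatic CAUTI, on the study wards per 1,000 patient bed-days, by site and year. State that events which are themselves the index episode count. Bed-days are already recorded for all ward patients and do not depend on culturing or on catheter use.

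Report the rate per 1,000 catheter-days as supporting, since the intervention may also reduce catheter use, and keep the 30-day per-episode measure as supporting.

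Cost: the culture-positive part of the count can be made from data already collected. Events without a positive culture need a small added flag in the existing chart review. Comparing that flag pre/post would require re-review of baseline charts already abstracted. The article describes the study as still in its baseline year, so the definition could be settled before the intervention begins. A ward-level count still misses events after transfer or discharge, and the report should say so.

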## Background

Urinary tract infection (UTI) is the single most common hospital-acquired infection, and many cases of nosocomial UTI are associated with an indwelling urinary catheter [1,2]. Urinary catheters bypass normal host defenses, and bacteriuria develops at the rate of approximately 5% per day; [3] nearly all individuals (98%) who are catheterized for 30 days or longer will have bacteriuria caused by one or more species of potentially pathogenic bacteria [4,5]. Furthermore, organisms causing catheter-associated urinary tract infection (CAUTI) are frequently resistant to one or more antibiotics [6,7]. In addition to these concerns regarding quality of care, annual incremental costs attributed to nosocomial CAUTI in 2002 were estimated to exceed $451 million [8]. Finally, since public reporting of nosocomial infections has become mandated in more than 30 states, [9] hospitals have strong incentive to reduce their rates of hospital-acquired CAUTI.

An important distinction exists between CAUTI and asymptomatic bacteriuria (ABU). CAUTI, as defined by the US Centers for Disease Control (CDC) and the National Healthcare Safety Network, involves symptoms (fever, urgency, frequency, dysuria, or suprapubic tenderness), in addition to microorganisms in the urine [10]. CAUTI requires antimicrobial treatment to relieve symptoms, while patients with ABU are, by definition, asymptomatic. Treatment of ABU in patients with an indwelling catheter does not improve morbidity or mortality, nor does it decrease the incidence of symptomatic CAUTI [11]. Use of antimicrobial agents to prevent or to treat catheter-associated ABU does lead to emergence of resistant flora, however [12]. Accordingly, evidence-based guidelines concerning ABU have stated that it is inappropriate to screen for or to treat ABU associated with the presence of a urinary catheter, with the exceptions of pregnant women and persons undergoing invasive urologic procedures [11,13]. The CDC campaign to prevent antimicrobial resistance in hospitalized patients likewise instructs clinicians to "treat infection, not colonization." [14] Unfortunately, a significant translation gap between evidence-based guidelines concerning management of ABU and clinical practice has been observed throughout the world [15,16]. Overtreatment of ABU is a quality, safety, and cost issue, particularly as unnecessary antibiotics lead to emergence of resistant pathogens [14,17].

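### The resistance outcome is called emergence but worded as any resistant isolate within 30 days, so it can include resistance already present and can fall simply because fewer cultures are sent

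*Protocol article*

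**What the plan says.** Table 3 (section Outcomes) ranks the clinical outcomes by importance. Its fifth row of six, complications of inappropriate antibiotics, contains "emergence of resistant organisms", with a footnote giving the window: "In 30 days following inappropriate antibiotic use in a given patient".

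The section on dependent variables for objective 1a treats the same item as safety monitoring: "we will monitor outcomes of bacteriuria at both sites for 30 days following the episode". The event there is "isolation of an organism resistant to the antibiotics given". Nothing in that wording refers to the susceptibility of the index isolate or asks that the later organism be new.

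Under Patients participating in the study, surveillance is by record review and captures "whether a urine culture was sent, and the results of any urine cultures sent". For each bacteriuria episode, "we collect information about patient demographics, the presence/absence of relevant symptoms and comorbidities, and type/duration of antibiotics given". Susceptibility of the index isolate is not in that list, and no follow-up culture is scheduled anywhere.

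For objective 1b the investigators predict that providers "they will recognize that urine cultures are frequently unnecessary in catheterized patients and thus, order fewer urine cultures". Under Analyses for objective 1, the remaining Table 3 outcomes are to be compared between sites by hierarchical regression when possible, and may be described only if fewer than 10 cases in total are expected.

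**The concern.** There are two separate difficulties.

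- **Name and measure differ.** Emergence implies a change from the index culture. The stated criterion needs only a later resistant isolate. If the index organism was already resistant to the drug given and grows again from a patient who is still catheterised, the criterion is met although nothing has emerged. The outcome then partly records mismatch between drug and organism instead of selection by unnecessary antibiotics.
- **Detection depends on the behaviour being changed.** A resistant organism enters the data only if someone sends a culture. The intervention aims to make clinicians send fewer urine cultures, at one site and from one point in time.

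Resistance is one of the main reasons the Background gives for reducing overtreatment. A lower figure at the intervention site would naturally be read as evidence that this harm had been reduced, when less looking could produce the same figure.

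**Working it through.** The article gives no rate, sample size or power for resistance, so there is no planned figure to reproduce. What follows compares the wording and then illustrates its consequences.

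**Inputs from the article**
- Event: a resistant isolate within 30 days (dependent variables for objective 1a).
- Source of cultures: those that clinicians send (Patients participating in the study).
- Expected direction of culturing: down at the intervention site (objective 1b).
- A 25% reduction, used in the sample size for objective 1b. It refers to the percentage of catheterised patients screened, not to re-culture after an episode.

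**Assumed inputs (the article gives none)**
- c = probability of a follow-up culture within 30 days, taken as 50%.
- r = probability that the index isolate was already resistant to the drug given and persists, taken as 10% to 30%.
- e = probability of true emergence among the rest, taken as 10%.

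**Formula.** Detected proportion of episodes = c × [r + (1 − r) × e].

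**Step 1: share of counted events that is not emergence** = r / [r + (1 − r) × e]
- r = 10%: 0.10 / 0.19 = 53%
- r = 20%: 0.20 / 0.28 = 71%
- r = 30%: 0.30 / 0.37 = 81%

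These shares show how sensitive the outcome is to r. They are not estimates for these hospitals.

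**Step 2: effect of less re-culturing when resistance is identical at both sites.** Let c fall by a fraction d at the intervention site, regardless of resistance status. The bracket cancels and the detected ratio is 1 − d:
- d = 10%: 0.90
- d = 25%: 0.75
- d = 50%: 0.50

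Example with r = 20% and d = 25%: control 0.50 × 0.28 = 14.0%; intervention 0.375 × 0.28 = 10.5%; ratio 0.75. The ratio does not depend on r, e or the starting value of c.

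**Step 3: does the design remove this?** The control site and baseline year deal with stable differences between hospitals and with trends common to both. A fall in culturing that the intervention causes occurs at one site after its start, so it remains in the comparison. Using the episode as the unit accounts for fewer index episodes being found, but not for fewer re-cultures per episode.

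**Side note on the window.** Table 3 starts the 30 days at inappropriate antibiotic use; the text starts them at the episode. Under the Table 3 start, the set of patients at risk itself shrinks as treatment falls, so a raw count would drop for that reason too.

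**The case against.** The strongest reply is that the criterion is one clause in a list of safety items in a condensed article. Read together with Table 3, it is compatible with an unstated comparison with the index isolate, which a fuller document might specify. That is fair as to intent: the article does not exclude such a comparison. But the criterion it does state does not measure the outcome it names.

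Several stronger readings are tempting and are not supported:
- **That index organisms are often resistant to the drug given.** The Background says that organisms causing CAUTI "are frequently resistant to one or more antibiotics". That concerns symptomatic infection and resistance to some antibiotic, not asymptomatic episodes and the drug prescribed. It makes pre-existing resistance plausible but does not show its frequency.
- **That the bias is 25%.** That figure plans for a fall in screening. Carrying it over to follow-up cultures is an assumption.
- **That detected resistance must fall with culturing.** The wording is not limited to urine, and the intervention targets unnecessary cultures. If the cultures dropped are those least likely to show resistance, or if isolates from other body sites count, the effect is smaller.
- **That patients who are not re-cultured are scored as event-free.** The article does not say how they are handled.

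It is also true that the culture rate is itself the second-ranked outcome, so a fall in culturing will be visible. However, the overall rate per catheter-day is not the proportion of episodes re-cultured within 30 days, which is what the reader needs beside this outcome. Finally, restricting the analysis to re-cultured patients conditions on a behaviour the intervention changes. That objection stands and limits the role such an analysis can have.

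**Conclusion.** The point holds in a limited form. As worded, the outcome includes resistance present at the index culture and is observable only after a clinician-initiated culture. For urine isolates the foreseeable direction of the detection effect favours the intervention site. Its size cannot be derived from the article: the ratios of 0.90, 0.75 and 0.50 hold only if re-culturing falls non-selectively by 10%, 25% or 50%, and the shares of 53% to 81% rest wholly on assumed rates. This is a lower-ranked safety outcome that may end up being described only. The primary outcome and its sample size are untouched. The change is still worth making, because it is cheap and prevents a fall in culturing from being reported as a fall in resistance.

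**What to change.** 1. Count an event only when the resistant organism is new, or when the index isolate was not resistant to the antibiotic given. Abstract index susceptibility from the same record.
2. List persistence of a resistant index organism as a separate item.
3. Report the proportion of episodes with any follow-up culture within 30 days, by site and year, beside the per-episode rate. State one starting point for the 30 days.
4. Give the rate among re-cultured patients only as a supporting analysis, and say that this subset is clinically selected and that the intervention may change the selection.
5. State in advance that a site difference in the unadjusted 30-day count will not be interpreted as reduced resistance.

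**Cost.** There is a modest abstraction step, since index susceptibility is not among the listed per-episode items, although the outcome already needs susceptibility for later isolates. There will be fewer events, which makes a descriptive report more likely. No additional patient procedure is needed.
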